**Methods:**

This protocol is drawn up in accordance with the SPIRIT guidelines and CONSORT Extension for Chinese herbal medicine formulas. This is a randomized, placebo-controlled, double-blind, multicenter trial. Two hundred twenty-eight adults with severe influenza are randomly assigned in a 1:1 ratio to *QZQG* or placebo for 7 days. All participants need to receive 1 day of screening before randomization, 7 days of intervention, and 21 days of observation after randomization. The primary outcome is the proportion of clinical improvement, defined as the proportion of patients who met the criteria of 3 points or less in the seven-category ordinal scale or 2 points or less in National Early Warning Score 2 within 7 days after randomization.

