#### Inclusion criteria

*The inclusion criteria are as follows:*
Diagnosis of influenza A and/or B by a positive Rapid Influenza Diagnostic Test (RIDT) or reverse transcriptase-polymerase chain reaction (RT-PCR).• Positive results from local tests are acceptable if conducted within the 24 h prior to screening.• A patient with a negative RIDT may be enrolled if influenza is suspected based on local surveillance data or if the patient reports contact with a known case of influenza within the prior 7 days and all other inclusion criteria are met.Granting of written informed consent.Male or female aged 18 to 65 years at the time of signing informed consent form.Ability to comply with the study protocol, in the investigator’s judgment.Participants who require hospitalization for severe influenza or acquire influenza during hospitalization, the severity of which requires an extension of hospitalization.Participants will require at least one of the following objective criteria of severe influenza: (i) duration with axillary temperature over 39 °C ≥ 3 days, accompanied by severe cough, sputum, blood sputum, or chest pain; (ii) rapid respiratory rate (≥30 times per minute), difficulty breathing and cyanosis of lips; (iii) arterial oxygen saturation (SaO2)/ pulse oxygen saturation (SPO2) ≤94% in room air condition; (iv) requires ventilation or supplemental oxygen to support respiration; (v) with only one complication related to influenza (e.g., pneumonia, central nervous system involvement, myositis, rhabdomyolysis, acute exacerbation of chronic kidney disease, asthma or chronic obstructive pulmonary disease (COPD), severe dehydration, myocarditis, pericarditis, exacerbation of ischemic heart disease).The time interval between the onset of symptoms and randomization is within 96 h. The onset of symptoms is defined as either time of the first increase in body temperature (≥ 38 °C) or time when the patient experiences at least one general or respiratory symptom.Conforming to the standard of TCM syndrome differentiation.

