### Outcomes measurements {12}

#### Primary outcome measure

The primary outcome is proportion of clinical improvement within 7 days. And clinical improvement is defined as at least one of the following criteria: (i) 3 points or less in the 7-category ordinal scale; (ii) National Early Warning Score 2 (NEWS2) of ≤2 and maintained for 24 h [23]. Seven-category ordinal scale was used in other influenza study [24–27]. The seven-category ordinal scale consisted of the following categories: 1, not hospitalized with resumption of normal activities; 2, not hospitalized, but unable to resume normal activities; 3, hospitalized, not requiring supplemental oxygen; 4, hospitalized, requiring supplemental oxygen; 5, hospitalized, requiring nasal high-flow oxygen therapy, noninvasive mechanical ventilation, or both; 6, hospitalized, requiring ECMO, invasive mechanical ventilation, or both; and 7, death. The UK’s National Early Warning Score 2 have good predictive abilities in patients with infections and sepsis [23], which are detailed in the Table 1.

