### Sample size {14}

Sample size calculations are based on the primary endpoint (the proportion of clinical improvement within 7 days after randomization). At the 5% significance level, a total of 101 patients per group is required to achieve 90% power and to determine an increase of 20% in the proportion of clinical improvement between *QZQG* group and the placebo group, assuming that the clinical improvement rate within 7 days after randomization of the placebo group receiving oseltamivir plus routine symptomatic treatment is about 50%. With an estimated dropout rate of 10–20%, a total of 228 patients are planned to be enrolled. If the initial hypothesis is not rejected, subsequent comparison is considered exploratory, and no conclusion is made.

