## Statistical methods

### Statistical methods for analyzing primary and secondary outcomes {20a}

The primary study analysis will occur when the last patient has either withdrawn or completed day 28 visit, and will be based on cleaned data for all patients up to and including this point. The clinical data will be managed and analyzed by the independent statisticians from a third party (School of Public Health, Fudan University,) in accordance with the statistical analysis plan. Data management and analysis will use SAS V.9.4 (SAS Institute, Cary, NC, USA).

All statistical inferences will be determined using two-sided tests. *P* < 0.05 will be considered significant, and 95% confidence intervals will be used. Data will be described as the mean, standard deviation, and confidence intervals. If necessary, minimum, maximum, P25, P75, and median values will be provided. Paired measurement data will also show the differences between the mean and standard deviation. When using nonparametric methods, median and mean values will be provided. Count data will be described using the frequency distribution and corresponding proportion. Qualitative information will be described using the positive rate, the number of positive cases, and the denominator.

Baseline data analyses (in FAS and PPS) will include demographic indicators and primary and secondary outcomes before intervention. Measurement data will be described using a *t*-test or *t*’ test (if the variance is absent). Count data will be described using the Pearson’s *χ*^2^ test. Rating data will be described using the two-sample Wilcoxon rank sum test.

Logistic regression model will be used to explore the efficacy (*QZQG* group and placebo group) and factors affecting efficacy. Dependent variable is the proportion of clinical improvement at day 7. In addition to drugs, independent variables also include the basic information and life behavior factors of participants. The basic information includes gender, height, weight, age, and underlying diseases that include chronic obstructive pulmonary disease, asthma, diabetes, hypertension, hyperlipidemia, hyperuricemia, cardiovascular disease, autonomic nervous dysfunction, lung cancer, other tumors, etc. Life behavior factors mainly include smoking and drinking.

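### The primary endpoint is an absolute threshold that inpatients not requiring oxygen already meet at day 0, so patients who have not changed can count as improved

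*Protocol article*

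**What the plan says.** The Protocol article, Primary outcome measure, states that "clinical improvement is defined as at least one of the following criteria: (i) 3 points or less in the 7-category ordinal scale". The second criterion is "National Early Warning Score 2 (NEWS2) of ≤2 and maintained for 24 h". Either one is enough, and neither refers to the patient's own starting value. The boundary on the ordinal scale lies between "3, hospitalized, not requiring supplemental oxygen; 4, hospitalized, requiring supplemental oxygen".

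Under Inclusion criteria, "Participants will require at least one of the following objective criteria of severe influenza". Five routes follow, and only route (iv) is a need for ventilation or oxygen. Route (i) is prolonged high fever with respiratory symptoms. Route (v) is "with only one complication related to influenza", with pneumonia and myositis among the examples. Neither the inclusion nor the exclusion list sets a minimum ordinal category or NEWS2 at entry. The exclusion list removes respiratory failure and conditions needing intensive care. The section on adherence {11c} says that all participants are inpatients.

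Two time rules appear. The Abstract counts "2 points or less in National Early Warning Score 2 within 7 days after randomization", and Primary outcome measure and Sample size {14} also use a 7-day window. Statistical methods {20a} says "Dependent variable is the proportion of clinical improvement at day 7".

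Sample size {14} plans 101 per group for 90% power at the 5% level to detect a 20-point increase, with the placebo rate for patients "receiving oseltamivir plus routine symptomatic treatment is about 50" per cent. The total is 228 after allowance for dropout.

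**The concern.** An endpoint called improvement should be one that a patient has not reached at randomization. Here an inpatient who does not require oxygen at entry is in category 3 and satisfies the first criterion on day 0. The two criteria are joined by OR, so the NEWS2 route can add responders but cannot remove this patient.

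Such patients add nearly the same count of successes to both arms. The difference between arms shrinks, and the reported proportion with clinical improvement includes people whose condition on the scale did not change. This is the only primary endpoint, it carries the sample size, and Sample size {14} makes later comparisons exploratory if it fails. A real effect could therefore be missed with no other route to a conclusion.

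**Working it through.** **1. Who meets the endpoint at day 0?**
- Route (i), fever with respiratory symptoms: no oxygen need implied, so category 3 is clearly possible.
- Route (v), one complication: category 3 is clearly possible for some (myositis, for example). Pneumonia may or may not need oxygen.
- Routes (ii), rapid breathing with dyspnoea and cyanosis, and (iii), low room-air saturation: unclear. The scale turns on requiring oxygen, so these patients may be scored 4 even before oxygen is started.
- Route (iv), ventilation or oxygen: category 4 or higher.

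**2. What happens to a patient in category 3 at day 0?**
- Criterion met at any time within 7 days: a responder in either arm, whatever happens later.
- Status at day 7: the patient can fail, but only by worsening. No change still counts as improvement.

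**3. Reproducing the planned size.** Pooled two-proportion formula with p1 = 0.50, p2 = 0.70, mean 0.60:

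n = [z(alpha) × √(2 × 0.6 × 0.4) + z(power) × √(0.5 × 0.5 + 0.7 × 0.3)]² / 0.20²

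- One-sided 5%: [1.645 × 0.693 + 1.282 × 0.678]² / 0.04 = 100.9, so 101. This is the stated figure.
- Two-sided 5%: [1.960 × 0.693 + 1.282 × 0.678]² / 0.04 = 124.0, so 124.

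**4. Dilution.** Let f be the share already in category 3 at entry. The article does not give it, so the values below are assumptions. Suppose these patients all count as successes and that 50% versus 70% holds among the rest. Then p(placebo) = f + (1 − f) × 0.50, p(QZQG) = f + (1 − f) × 0.70, and the difference is 0.20 × (1 − f). Power is exact binomial power of the Pearson test at 101 per group; n is from the formula in step 3.

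| f | Placebo vs QZQG | Difference (points) | Power, one-sided 5% | Power, two-sided 5% | n per group for 90%, one-sided / two-sided |
|---|---|---|---|---|---|
| 0 | 50% vs 70% | 20 | 90% | 84% | 101 / 124 |
| 10% | 55% vs 73% | 18 | 85% | 76% | 120 / 148 |
| 20% | 60% vs 76% | 16 | 79% | 69% | 144 / 177 |
| 30% | 65% vs 79% | 14 | 72% | 60% | 175 / 215 |
| 40% | 70% vs 82% | 12 | 64% | 52% | 216 / 265 |
| 50% | 75% vs 85% | 10 | 56% | 43% | 273 / 335 |

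**5. The other reading of the 50%.** If the planned 50% versus 70% already includes these patients, the rates among the rest are (0.50 − f)/(1 − f) and (0.70 − f)/(1 − f). At f = 30% these are 0.20/0.70 = 29% and 0.40/0.70 = 57%, so the effect needed among patients who can still improve is 29 points, not 20.

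**The case against.** Several points on the other side are sound and limit the claim.

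- **Oxygen need.** A reader might infer that every patient not on oxygen at entry, under four of the five routes, already meets the endpoint. The documents do not support that. The scale asks whether oxygen is required, and patients entering by routes (ii) and (iii) may well be scored 4. The clear cases are route (i) and part of route (v).
- **No information at all.** A reader might infer that these patients carry no information on treatment. That holds only for the 7-day-window wording. If status at day 7 is analysed, deterioration counts as failure and dilution is incomplete, so the table shows the worst case for each f. It is also unclear whether the 24-hour requirement applies to the ordinal criterion; a patient who stays stable would meet it either way.
- **Placebo rate above plan.** A reader might infer that the placebo rate must exceed 50%. The article gives about 50% for the whole placebo group and does not say what mix of patients lies behind it. If that mix includes category 3, the overall rate need not rise; step 5 then applies.
- **Details left to the full documents.** The article states the endpoint and the eligibility criteria explicitly, and the mismatch lies between those two statements. For the secondary outcome of time to symptom improvement, the article does require pre-existing symptoms to improve from baseline; the primary endpoint has no such condition.

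**Conclusion.** The structural defect stands: some eligible patients meet the primary endpoint at randomization, and nothing in the article sets a baseline floor or handles them separately. Its size cannot be known from the article, because f is not given. For assumed f of 10% to 50%, complete dilution and 50% versus 70% among the rest, the difference falls to between 18 and 10 points. Power at 101 per group falls from 90% to between 85% and 56% on the one-sided basis that reproduces 101, or from 84% to between 76% and 43% two-sided.

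Two stronger conclusions should be avoided. The gap between 90% and 84% at f = 0 is not caused by this endpoint: 101 matches only a one-sided 5% test, while Statistical methods {20a} specifies two-sided tests, which is a separate issue. Nor does the defect make a false positive more likely. It pulls towards no difference, so the harm is lost power and a label that misdescribes what is counted.

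**What to change.** Record the ordinal category and NEWS2 at day 0 and amend the primary endpoint so that a criterion counts only if it was not met at baseline:
- category 3 or less counts only from a baseline category of 4 or more;
- NEWS2 of 2 or less held for 24 hours counts only from a baseline NEWS2 above 2;
- both routes stay open to everyone, so a patient in category 3 with a raised NEWS2 can still succeed on NEWS2.

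A patient who meets both criteria at day 0 cannot then succeed. The simple alternative is to restrict the primary analysis to patients who meet neither criterion at baseline and to report the others separately. That set is fixed by pre-treatment data, so the randomized comparison is kept.

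In the same amendment, choose one time rule (within 7 days or at day 7) and use it throughout, and restate the 50%/70% assumption and the power for the amended endpoint.

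Cost: new endpoint wording, a derived baseline variable and restated planning figures. The assessment burden is small, since the participant timeline already has vital signs and temperature at day 0. The success rate will be lower, or the primary analysis set smaller. For example, if 30% were set aside, 101 analysable patients per group would need 101/0.70 = 144.3, so 145 per group before dropout, against the 114 per group (228/2) now planned including dropout.

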**Table 1 Tab1:**
[figure not shown]
National Early Warning Score 2 (NEWS2)

NEWS2: (i) The oxygen saturation should be scored according to either the SpO2 Scale 1 or 2 presented in the table above. The SpO2 Scale 2 is for patients with a target oxygen saturation requirement of 88–92% (e.g., in patients with hypercapnic respiratory failure related to advanced lung diseases, such as chronic obstructive pulmonary disease [COPD]). This should only be used in patients confirmed to have hypercapnic respiratory failure by blood gas analysis on either a prior or their current hospital admission. The decision to use the SpO2 Scale 2 should be made by the treating physician and should be recorded in the eCRF. In all other circumstances, the SpO2 Scale 1 should be used. (ii) For physiological parameter “Air or Oxygen?”: Any patients requiring the use of oxygen or other forms of ventilation to maintain oxygen saturations and support respiration should be assigned a score of 2. (iii) The consciousness level should be recorded according to the best clinical condition of the patient during the assessment. Patients who are assessed as “Alert” (A) should be assigned a score of 0. Patients assessed as “New Confusion” (C), “Responsive to Voice” (V), “Responsive to Pain” (P), or “Unconscious” should be assigned a score of 3

#### Secondary outcome measure

Secondary outcomes are the following:
Time to clinical improvement of symptoms (TTCIS) [time frame: baseline to day 14].Participants assessed the severity of 7 influenza-associated symptoms (cough, sore throat, headache, nasal congestion, feverishness/chills, muscle/joint pain, and fatigue) on a 4-point scale (0 = no symptoms, 1 = mild, 2 = moderate, and 3 = severe). TTCIS was defined as the time from the start of treatment to the time when all influenza symptoms were alleviated, as defined below, for a duration of at least 21.5 h:• Pre-existing symptoms (cough, fatigue, or muscle/joint pain that existed prior to influenza) that were worse at baseline must have improved at least 1 point from baseline.• New symptoms must have alleviated, defined as a symptom score of none (0) or mild (1).Time to defervescence (TTD) [time frame: baseline to day 14].Time to defervescence includes defervescence onset time and the time to complete defervescence. Defervescence onset time is defined as the time from the start of treatment to the time when the body temperature decreases to ≤37.3 °C. And complete defervescence is defined as the time from the start of treatment to the time when the temperature of ≤37.3 °C sustained for ≥ 24 h [14, 28].Percentage of participants with 2 or more Influenza-related complications [time frame: baseline to day 28].Secondary influenza complications include pneumonia, encephalitis, meningitis, encephalopathy, myelitis, Guillain-Barré syndrome, myocarditis, pericarditis, myositis, and septic shock.Percentage of participants whose symptoms were improved at each time point [time frame: 12, 24, 36, 48, 72, 96, 120, 144, and 168 h after the initial dose of study treatment]. The criteria for improvement of influenza symptoms have been described above.Percentage of participants reporting normal temperature at each time point [time frame: 12, 24, 36, 48, 72, 96, 120, 144, and 168 h after the initial dose of study treatment]. Defined as the percentage of participants whose axillary body temperature dropped to equal or less than 37.3 °C after the initiation of the study treatment.Body temperature at each time point [time frame: 12, 24, 36, 48, 72, 96, 120, 144, and 168 h after the initial dose of study treatment]. Participant’s self-measured axillary temperature using an electronic thermometer.Percentage of participants requiring systemic antibiotics for infections secondary to influenza [time frame: day 2 to day 28].Percentage of participants with adverse events (AEs).Inpatient length of stay defined as number of days in hospital [time frame: day 2 to day 28].Median time (days) receipt of oxygen [time frame: day 2 to day 28].

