#### Relevant concomitant care permitted or prohibited during the trial {11d}

Considering ethical requirements of IRB, all enrolled patients need to receive one oseltamivir capsule (75 mg/per capsule), twice a day for 7 days [6]. Since patients with severe influenza in the all centers of China are hospitalized, the necessary intravenous fluid therapy is allowed. When the body temperature of a participant rises to higher than 39.0 °C, physical cooling and antipyretics are allowed to be used to reduce the fever. The treatments for hypertension, diabetes, cerebral infarction, and other underlying diseases are allowed as well. The doctors of the trial team must carefully record the name, dose, usage, and duration of the concomitant drugs or treatment in the case report form (CRF).

However, no other antivirals for influenza are allowed during the study period. Adjunctive therapies such as corticosteroids were prohibited. In addition, it is absolutely forbidden to take other Chinese herbal medicines and Chinese patent medicine during the study period or within 14 days before randomization. When the patients have drug-related adverse events or serious complications such as viral pneumonia, hepatoprotective drug, antibacterials, and other necessary treatments are completely allowed and recorded.

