**Efficacy and safety assessment**					
▪ Vital signs (heart rate, blood pressure, breathing rate and oxygen saturation)	**x**	**x**	**x**	**x**	**x**
▪ Electrocardiograph	**x**	a			**x**
▪ Chest radiograph	**x**	a			**x**
▪ Laboratory inspection	**x**	a			**x**
▪ Record adverse events	**x**	**x**	**x**	**x**	**x**
▪ Body temperature	**x**	**x** (Measured at 4, 8, 12, 16, 20 and 24 o'clock)	**x**	**x**	**x**
▪ Record influenza symptoms	**x**	**x**	**x**	**x**	**x**
▪ Use of antibiotics		**x**	**x**	**x**	**x**

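### Defervescence onset and the time-point temperature outcomes count readings taken just after permitted antipyretics or cooling, which mainly attenuates any true QZQG effect on fever

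*Protocol article*

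**What the plan says.** The protocol article, under the secondary outcome measures, splits time to defervescence into two parts. The first is onset: "Defervescence onset time is defined as the time from the start of treatment to the time when the body temperature decreases to ≤37.3 °C". The second is the sustained version: "complete defervescence is defined as the time from the start of treatment to the time when the temperature of ≤37.3 °C sustained for ≥ 24" hours.

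Two further outcomes are taken at 12, 24, 36, 48, 72, 96, 120, 144 and 168 h after the first dose. One is the share with normal temperature: "Defined as the percentage of participants whose axillary body temperature dropped to equal or less than 37.3 °C after the initiation of the study treatment". The other is body temperature itself: "Participant’s self-measured axillary temperature using an electronic thermometer".

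The participant timeline (Table 2) fixes the readings on days 1 to 7: "Measured at 4, 8, 12, 16, 20 and 24 o'clock".

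The section on concomitant care {11d} says that above 39.0 °C "physical cooling and antipyretics are allowed to be used to reduce the fever". This applies to both arms. The same section requires the name, dose, usage and duration of concomitant treatment to be entered in the CRF.

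The statistical methods {20a} name repeated-measures analysis of variance and covariance analysis for quantitative variables, without mentioning antipyretic use. The section on analysis populations {20c} assigns multiple imputation to missing data. Neither section says how a reading taken after rescue is to be treated.

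**The concern.** An antipyretic or physical cooling can bring a temperature down for a few hours without ending the febrile illness. With readings every 4 h, a patient who spikes to 39.5 °C, is given an antipyretic, reads 37.2 °C at the next scheduled time and then spikes again has reached defervescence onset under the definition as written. The clock stops for good at that reading. The same reading, if it falls at a scheduled time point, counts as a normal temperature and enters the mean temperature.

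Rescue depends on fever after randomization. If QZQG shortens fever, more placebo patients exceed 39.0 °C, more of them may be given rescue, and more placebo readings are pulled down. The arms then look more alike than they are.

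The Discussion says that the secondary endpoints are there to show consistency with the primary endpoint. Fever outcomes that are diluted in this way serve that purpose poorly.

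**Working it through.** The article gives no figure for the temperature outcomes, so there is nothing to reproduce. The check has two parts.

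**1. The definitions against the rescue allowance**

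| Outcome | Duration required | Rescue-free condition | Exposure |
|---|---|---|---|
| Defervescence onset | none | none | one dip after rescue is enough |
| Normal temperature at 12–168 h | none | none | any dip at a time point |
| Body temperature at 12–168 h | not applicable | none | the reading is lowered |
| Complete defervescence | 24 h or more | none | a dose given just before the run |

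The last row differs because rescue is permitted only above 39.0 °C. A patient who stays at or below 37.3 °C for 24 h never meets that trigger during the run, and a reading above 39.0 °C would end the run.

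**2. Size, on assumed rates**

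None of the rates below comes from the article.

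*Afebrile percentage at one time point.* Let p be the proportion truly afebrile, r the share of still-febrile patients given rescue, and q the chance that rescue brings the reading to 37.3 °C or below. Then

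observed proportion = p + (1 − p)·r·q.

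Take p = 0.30 (placebo) and 0.45 (QZQG), a true difference of 15 points. With r = 0.40 in both arms and q = 0.5:

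- placebo: 0.30 + 0.70 × 0.40 × 0.5 = 0.440
- QZQG: 0.45 + 0.55 × 0.40 × 0.5 = 0.560
- observed difference: 12.0 points

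| True p, placebo / QZQG | r, placebo / QZQG | Difference at q = 0.5 | Difference at q = 0.8 |
|---|---|---|---|
| 0.30 / 0.45 | 0.40 / 0.40 | 12.0 | 10.2 |
| 0.30 / 0.45 | 0.40 / 0.20 | 6.5 | 1.4 |
| 0.30 / 0.45 | 0.60 / 0.30 | 2.2 | −5.4 |
| 0.30 / 0.30 | 0.40 / 0.20 | −7.0 | −11.2 |
| 0.30 / 0.30 | 0.30 / 0.40 | +3.5 | +5.6 |

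*Defervescence onset.* Assume true onset is lognormal with medians of 72 h (placebo) and 48 h (QZQG) and log-SD 0.6. In a share s of patients, a rescue-induced normal reading falls uniformly between 4 and 24 h and replaces a later true onset. When the observed median exceeds 24 h it is

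median = M·exp{0.6·Φ⁻¹[1 − 0.5/(1 − s)]}, where M is the true median.

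For placebo with s = 0.30: 1 − 0.5/0.7 = 0.286, Φ⁻¹ = −0.566, and 72·exp(−0.340) ≈ 51 h. Medians below 24 h were solved numerically from the same model.

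| s, placebo / QZQG | Placebo median | QZQG median | Difference |
|---|---|---|---|
| 0 / 0 | 72.0 h | 48.0 h | 24.0 h |
| 0.20 / 0.10 | 59.5 h | 44.1 h | 15.3 h |
| 0.30 / 0.30 | 51.3 h | 34.2 h | 17.1 h |
| 0.30 / 0.20 | 51.3 h | 39.6 h | 11.6 h |
| 0.40 / 0.30 | 40.3 h | 34.2 h | 6.1 h |
| 0.50 / 0.50 | 23.4 h | 21.9 h | 1.5 h |
| 0.50 / 0.35 | 23.4 h | 30.9 h | −7.5 h |

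When both true medians are 72 h, shares of 0.30 and 0.20 give 51.3 h and 59.5 h, a spurious difference of about 8 h in favour of placebo.

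In both models, equal rescue shrinks the difference but keeps its sign in every case run. The sign changes only when rescue is both frequent and clearly unequal between the arms.

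**The case against.** The strongest reply is that counting temperature regardless of permitted, blinded care open to both arms is a legitimate treatment-policy choice, and that handling of concomitant medication is commonly left to an analysis plan, which is not shown here. That stands for how rescue is analysed. It does not settle the outcome definition, because the article itself fixes the threshold, the time points and the durations. It sets 24 h for complete defervescence and 21.5 h for symptom alleviation, but nothing for onset. Nor does it declare a treatment-policy aim.

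Other points limit the concern, and they stand:

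- These are secondary outcomes.
- If an effective QZQG leads to more rescue on placebo, the bias runs towards no difference. It would not create a false benefit.
- How often patients exceed 39.0 °C after randomization is unknown. More than 39 °C for at least 3 days is only one of five alternative severity criteria, and the TCM pattern requires high fever of everyone without giving a threshold.

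A reader might infer two stronger claims. One is that these outcomes measure rescue use instead of the QZQG effect, or reverse it. Reversal appears only at high and unequal assumed rates, for which the article offers no support. The other is that repeated antipyretics could hold down a 24 h run and so produce complete defervescence. Dosing within such a run would fall outside the stated allowance, since that requires a temperature above 39.0 °C.

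**Conclusion.** The point holds for defervescence onset and for the percentage with normal temperature, and body temperature at each time point is affected in the same way. As written, a short dip after rescue counts as fever resolution.

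The supported consequence is mainly attenuation. With equal rescue at the assumed rates, a 15-point difference falls to 10.2–12.0 points. A 24 h difference in median onset falls to about 17 h when 30% of each arm have an early rescue-induced normal reading. These sizes rest wholly on assumed rescue rates and on the assumed success of rescue in bringing a reading to 37.3 °C. Reversal or a spurious difference is possible but needs frequent or unequal use that the article does not document.

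Complete defervescence is largely protected, and the primary outcome is not one of these temperature endpoints. The change is worth making because it is cheap, but it does not threaten the trial's main conclusion.

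**What to change.** In the secondary outcome definitions:

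- **Onset and normal-temperature percentage:** count a reading as afebrile only if no antipyretic or physical cooling was used within one fixed preceding interval, set before unblinding. Score readings inside that interval as not afebrile. Do not set them to missing, because multiple imputation would then fill gaps that are informative about fever.
- **Body temperature at each time point:** keep all readings, and add a sensitivity analysis that handles those taken after rescue.
- **Recording and reporting:** add the clock time of antipyretic and cooling use to the CRF, which already takes name, dose, usage and duration, and report rescue use by arm.

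Onset can stay at its present rank beside complete defervescence. The rule on when rescue may be given is not touched.

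The cost is a few sentences of definition and one CRF field. Stated onset times will lengthen slightly and afebrile percentages will fall slightly, because a patient whose fever has truly ended inside the interval is counted a little late.
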